## Abstract

**Background:**

Acute respiratory illness (ARI) is the most common cause of acute presentations and hospitalisations of young Indigenous children in Australia and New Zealand (NZ). Environmental tobacco smoke (ETS) from household smoking is a significant and preventable contributor to childhood ARI. This paper describes the protocol for a study which aims to test the efficacy of a family-centred tobacco control program about ETS to improve the respiratory health of Indigenous infants in Australia and New Zealand. For the purpose of this paper 'Indigenous' refers to Australia's Aboriginal and Torres Strait Islander peoples when referring to Australian Indigenous populations. In New Zealand, the term 'Indigenous' refers to Māori.

**Methods/Design:**

This study will be a parallel, randomized, controlled trial. Participants will be Indigenous women and their infants, half of whom will be randomly allocated to an 'intervention' group, who will receive the tobacco control program over three home visits in the first three months of the infant's life and half to a control group receiving 'usual care' (i.e. they will not receive the tobacco control program). Indigenous health workers will deliver the intervention, the goal of which is to reduce or eliminate infant exposure to ETS. Data collection will occur at baseline (shortly after birth) and when the infant is four months and one year of age. The primary outcome is a doctor-diagnosed, documented case of respiratory illness in participating infants.

**Discussion:**

Interventions aimed at reducing exposure of Indigenous children to ETS have the potential for significant benefits for Indigenous communities. There is currently a dearth of evidence for the effect of tobacco control interventions to reduce children's exposure to ETS among Indigenous populations. This study will provide high-quality evidence of the efficacy of a family-centred tobacco control program on ETS to reduce respiratory illness. Outcomes of our study will be important and significant for Indigenous tobacco control in Australia and New Zealand and prevention of respiratory illness in children.

**Trial registration:**

Australian New Zealand Clinical Trials Registry (ACTRN12609000937213)

## Background

Globally, acute respiratory infections (ARI) cause more deaths and hospitalisations among Indigenous children compared with their age-matched counterparts; the greatest impact is among young children aged 0-4 years [1]. Specifically, in Australia and New Zealand (NZ), ARI is the leading cause of morbidity among Indigenous children, resulting in more hospitalisations than any other cause [2-4].

While there are multiple socioeconomic determinants of ARIs among Indigenous children, environmental tobacco smoke (ETS) exposure is arguably the most readily amenable to modification. The adverse health effects of ETS are well documented, especially its association with respiratory illness. The association between parental smoking and childhood respiratory disease is strongest at younger ages [5]. In children, exposure to ETS is causally related to the frequency and severity of respiratory illness (especially lower respiratory illness), as well as otitis media and chronic middle ear effusion [6,7]. Exposure to ETS during early childhood is also associated with an increased risk and/or worsening of pre-existing asthma symptoms among children [8,9]. Additionally, childhood ETS exposure is associated with sudden infant death syndrome (SIDS) [10].

In recognition of the damaging health effects of ETS, the World Health Organization (WHO) has prioritised the need to reduce parental smoking as a core component of improving health and development in early childhood [11]. This is especially important among socioeconomically disadvantaged populations where smoking rates among adults are higher, compared to more advantaged groups. Indigenous Australians and Māori New Zealanders are twice as likely to smoke as their non-Indigenous counterparts [12,13]. High smoking rates mean Indigenous children in these countries suffer a greater burden of ETS exposure. Australian data indicate that approximately one third of Indigenous children aged 0-14 years live in households with a regular smoker who smokes indoors compared with 9% of non-Indigenous young people [14]. While there has been a significant fall in the proportion of Maori households where smoking is permitted indoors, age-adjusted data from the 2006/7 NZ Health Survey found that Māori children and children living in neighbourhoods of high deprivation had twice the risk of exposure to ETS in their home compared to the total population of children surveyed [15].

Despite the recognition of the adverse child health effects of ETS and the scale of the problem among disadvantaged populations in particular, exposure reduction in homes is a relatively recent area of scientific study [16]. A recent systematic review of family and carer tobacco control programs for reducing children's exposure to ETS reported that of 36 studies that met inclusion criteria, 11 demonstrated a statistically significant intervention effect [17]. While the authors of this review [17] concluded that there was insufficient evidence to show which interventions were most effective, there does appear to be modest empirical support for more intensive counselling approaches for parents in this context and for interventions which focus on changing participants' attitudes and behaviours (i.e. premised on a theory of behaviour change), rather than just aiming to change knowledge alone. Notably, recent qualitative research on smoking in remote Northern Territory Indigenous communities found that Indigenous parents and carers are concerned about the health effects of ETS [18]. Moreover, their primary motivation to quit was the health of their children, in addition to positive role modelling. Among those who had failed to quit, some were already taking positive steps to minimise the exposure of their children to tobacco smoke. This reflects the importance afforded to the wellbeing of the family and in particular the fulfilment of familial responsibilities towards the care and protection of children among Indigenous Australians [19]. NZ Māori similarly have quit for the benefit of their children, with health and cost as other primary motivators to quit [20,21]. These data suggest that a family based tobacco control intervention, which was not predicated on adults quitting smoking and was focused around the welfare of children, may be particularly effective among this population.

This study aims to test the efficacy of a culturally appropriate, family-centred tobacco control program about ETS to improve the respiratory health of Indigenous infants in Australia and NZ.

### Hypothesis

Infants (<12 months) of Indigenous mothers/caregivers who receive an intensive family-centred tobacco control program about ETS, compared with 'usual care,' will have fewer health care presentations for respiratory illness.

## Methods/Design

### Objectives

The primary objective of this study is to determine the efficacy of a family-centred tobacco control program about ETS, to reduce health care presentations for respiratory illness in Indigenous infants in the first year of life. Secondary objectives include assessment of the effect of such a program on a range of measures of infant ETS exposure, including mother/caregiver's self-report of infant exposure to ETS and implementation of smoking restrictions in the home and/or car, infant urinary cotinine, household smoking status, mother/caregiver's smoking cessation and quit attempts. A process evaluation of the family-centred tobacco control program will also be undertaken.

### Study Design

This study will be a parallel, randomized controlled study with allocation concealed from the study researchers. Participants will be randomly allocated to one of two study arms: the 'intervention' group who will receive the tobacco control program about ETS exposure over three home visits in the first three months of the infant's life, or the control group who will receive 'usual care' (i.e. they will not receive the tobacco control program). IHWs will be trained to deliver the intervention program, the goal of which is to reduce or eliminate exposure of infants to ETS. Data collection will occur at baseline (shortly after birth), and when the infant is four months and one year of age. The primary outcome of interest is the rate of health care presentations for doctor-diagnosed respiratory illness. Figure 1 outlines the flow of participants through the study.

**Figure 1 F1:**
[figure not shown]
**Flowchart for a randomized controlled trial of a family tobacco control program about ETS to reduce respiratory illness in Indigenous infants**.

### Study Population

This study will be conducted in Darwin City and the Greater Darwin area in the Northern Territory, Australia; and within the Counties Manukau District Health Board region, Manukau City, NZ. The target populations for this study are Indigenous families who reside in these two geographical areas. The sampling unit is Indigenous newborn infants and their mothers/primary caregivers (aged 16 years and over).

#### Inclusion Criteria

Infants will be eligible for inclusion if:

• They are aged between 0-5 weeks. (We will review our recruitment rate four months after the trial has commenced. If we find that we are not meeting our enrolment targets, we will consider extending our recruitment to include infants aged 5-10 weeks. This will allow us to approach mothers and their infants at 6-8 weeks when they present at community health clinics for their first immunizations.)

• Their mother/caregiver is Indigenous (defined by maternal self-identification).

• Their mother/caregiver is aged 16 years or over.

• Their mother/caregiver currently smokes or the infant lives in a household where there is at least one other person who smokes (defined as smoking at least weekly).

• Their mother/caregiver plans to reside permanently with the infant in Darwin or Greater Darwin areas of Australia or within the Counties Manukau District Health Board region, Manukau, NZ.

• Their mother/caregiver has given signed written consent to participate in this research study.

• Their mother/caregiver has given signed written consent for study staff to access the infant's health records.

• They are a singleton or the first born in a multiple pregnancy delivery.

• Their mother/caregiver speaks English and/or Māori.

#### Exclusion Criteria

Infants will be excluded from the trial if:

• They have serious neonatal respiratory complications (i.e. they require oxygen for >24 hours during their postnatal hospital stay).

• They have other serious neonatal complications (e.g. seizures, significant sepsis).

• They have major organ abnormalities (i.e. cardiac disease, congenital lung/diaphragm abnormalities, chromosomal abnormality or syndrome e.g. Down's syndrome).

The above exclusion criteria are because these infants will be given intense interventions to reduce ETS exposure regardless. Infants will also be excluded if:

• Their mother/caregiver has previously been recruited in this research study.

• They live in the same household as a mother/caregiver who has previously been recruited in this study.

### Randomisation: allocation concealment and sequence generation

Participants will be randomized by computer with stratification using permuted blocks by country (Australia, NZ) and infant age (0-5 weeks, >5-10 weeks). This will ensure a balance in these key prognostic indicators between the intervention and control groups. All participants (i.e. the infants) will be assigned a unique registration number allocated by a central computer following the submission of their details on a web-based form.

### Blinding

This is an assessor blinded trial, with only the study researchers assigning the major primary and secondary outcome measures and trial statisticians blinded to group assignment. Research assistants, who will be responsible for collecting the minor outcome measures will accompany the health workers to the participants' homes for all visits and thus cannot be blinded. The primary outcome will however be a double-blinded measure.

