### Proposed intervention

Globally, Indigenous notions of health and illness are generally defined more broadly than a Western biomedical definition that focuses more often on physical health or the absence of disease [22]. In Australia, the National Aboriginal Health Strategy, [[23], p.x] defines Indigenous 'health' holistically as the physical, social, emotional, and cultural wellbeing of the individual and the community. In NZ, Te Whare Tapa Wha, a widely used Māori model of health is based on the four-sided whareuni or meeting house. It incorporates tinana (physical body), hinengaro (psychological), whānau (family and community), and wairua (spirit) [20]. Balance between these dimensions is required in order to maintain stability and good health. Poor health develops when there is a breakdown in the harmony of these four realms within the individual or in their relationship to the wider environment [20].

In this study, the intervention program about ETS will be framed around an Indigenous model of health promotion, which attends to the psychological, physical, spiritual and cultural wellbeing of the individual and the family/community, as it relates to this project. In NZ, Te Whare Tapa Wha will be used. This model has been applied to understanding Māori smoking cessation behaviour [20] and for guiding the development of culturally appropriate smoking cessation programs and strategies [24]. In Australia, the model will draw on similar concepts. The counselling/psychological component of the intervention program is founded on social cognitive theory and motivational interviewing.

Participants will be told that they will be randomly assigned to a group that receives 'usual care', or a group that receives extra home visits by an IHW, and that a variety of study measurements will be taken over a 12-month period.

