### Outcome measures

Primary Outcome: *Rate of health provider presentations for new primary episodes of ARI in the first year of life*.

All participating infants will be evaluated at baseline and when the infant is four and 12 months old, for the occurrence of medically attended acute respiratory illnesses (MAARI). These are defined as new onset events, including a change from the child's baseline medical status, referable to the upper and/or lower respiratory tracts. To identify episodes of ARI mothers/caregivers will be asked at baseline, and when the infant is four and 12 months old, whether their child has had any presentation to the clinic or hospital and the names of the clinics attended. Research assistants will collect the source data relevant to the primary outcome measures, so will review the individual child's health provider and hospital clinic records (parental consent will be obtained prior to accessing records). Source documents will be photocopied, de-identified, labeled with the participant registration, and stored with the trial records. Two clinicians at each study centre will review the records and confirm documented respiratory illnesses without knowing the group allocation of the individual children. MAARI events will be evaluated by these clinicians to determine whether they are medically-attended upper respiratory infection (URI), lower respiratory infection (LRI) and/or otitis media infection (based on the definitions in Additional file 1: Table S1). Conflict will be resolved by discussion and consensus between the two clinicians. Intra-rater and inter-country reliability testing will be performed on primary outcome data from 20 participants at each site. Information on antibiotic use for the treatment of medically attended URI, LRI or otitis media events will not be collected.

Major secondary outcomes:

▪ *Rate of hospitalizations for ARI*: same case definition as primary outcome measure.

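### The primary outcome is called double-blinded, but only the classification of collected records and the analysis are blinded; the finding and copying of records is not

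*Protocol article*

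**What the plan says.** The Blinding section calls the trial assessor-blinded, with "only the study researchers assigning the major primary and secondary outcome measures and trial statisticians blinded to group assignment". It then turns to the field staff and their task: "Research assistants, who will be responsible for collecting the minor outcome measures". Of these assistants it adds that they "will accompany the health workers to the participants' homes for all visits and thus cannot be blinded". It closes with the statement that "The primary outcome will however be a double-blinded measure".

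The Outcome measures section sets out how events are found. "To identify episodes of ARI mothers/caregivers will be asked at baseline, and when the infant is four and 12 months old", the question being "whether their child has had any presentation to the clinic or hospital and the names of the clinics attended". Next, "Research assistants will collect the source data relevant to the primary outcome measures", which they do by going through each child's clinic and hospital records. The documents are photocopied, de-identified and labelled with the registration number. Two clinicians at each centre then confirm and classify the illnesses without knowing allocation.

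On awareness of allocation, the Proposed intervention section says participants will be told that they may be assigned to usual care "or a group that receives extra home visits by an IHW". The programme is three face-to-face home visits, so a family knows whether it is receiving it.

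The Data monitoring section has all electronic ARI endpoint data checked against source data.

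**The concern.** The primary outcome is a count of presentations per infant. A count can be distorted at two points: which presentations enter the file, and how those in the file are classified. The article blinds the second and calls the whole measure double-blinded. The first is in the hands of people who know the arm: the caregiver, whose answers direct the search, and the assistant who does the searching and copying.

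If capture differs between arms, the rate ratio shifts by the same proportion, and blinded adjudication cannot restore a visit that was never photocopied. The label would also carry into the trial report and give readers an assurance that the design does not provide. The Blinding section, which is where a reader would look, does not mention that assistants retrieve the primary-outcome records.

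**Working it through.** **Who knows the arm at each step**

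| Step | Done by | Knows the arm? | Section |
|---|---|---|---|
| Names the providers attended | Caregiver | Yes, the programme is overt | Proposed intervention; Outcome measures |
| Searches and copies records | Research assistant | Yes, attends all home visits | Blinding; Outcome measures |
| Classifies the copies | Two clinicians per centre | No | Outcome measures |
| Analyses the counts | Statisticians | No | Blinding |
| Checks endpoint data against source | Monitor | Not stated; the check as described uses collected source | Data monitoring |

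The first two steps decide which presentations can be counted, and neither is blinded. The last three work only on what those two steps deliver.

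**The plan's own power figure**

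Inputs from the Sample size section: control mean 3 presentations per year, Poisson, 5% significance. From Treatment effects: two-tailed tests. From the Abstract: half of participants in each arm.

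SE(ln RR) = √[(1/λ₀ + 1/λ₁)/n per arm]; power ≈ Φ(|ln RR|/SE − 1.96).

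- N = 190, λ₁ = 2.25: SE = √[(0.3333 + 0.4444)/95] = 0.0905; |ln 0.75| = 0.2877; power = Φ(3.18 − 1.96) ≈ 89%.
- N = 380, λ₁ = 3 × 0.82 = 2.46: SE = √[(0.3333 + 0.4065)/190] = 0.0624; |ln 0.82| = 0.1985; power = Φ(3.18 − 1.96) ≈ 89%.

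Both agree with the stated 90% to within about one percentage point, so the same model can be used below.

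**Illustration of sensitivity**

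The documents give no figure for differential capture. The 5% and 10% below are assumptions, with full capture in the control arm and N = 380.

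No true effect, fewer presentations captured in the intervention arm:

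- 5% fewer: λ₁ = 2.85, apparent RR 0.95. SE = √[(0.3333 + 0.3509)/190] = 0.0600; |ln 0.95|/SE = 0.0513/0.0600 = 0.855. Two-sided rejection = Φ(0.855 − 1.96) + Φ(−0.855 − 1.96) ≈ 0.137, about 14% against a nominal 5%. At N = 190 the figure is about 9%.
- 10% fewer: apparent RR 0.90, rejection about 41% (about 23% at N = 190).

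True RR 0.82, relatively more captured in the intervention arm:

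- 5% more: apparent RR 0.82 × 1.05 = 0.861, power about 68% instead of 89%.
- 10% more: apparent RR 0.82 × 1.10 = 0.902, power about 40%.

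These show how a trial aimed at an 18% reduction responds to modest differences in capture. They do not estimate what would happen in this trial.

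**The case against.** The Blinding section is open about who is unblinded. Its closing sentence may be loose wording for two blinded assessors. That is a fair reading of intent, but it is not the usual meaning of the term, and it conflicts with the section's own list of who is blinded.

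The stronger objection concerns the bias. Events are documented presentations confirmed by blinded clinicians, both arms are asked the same question at the same three time points, and a single named clinic opens that clinic's record for the child. Differential loss then mainly requires a whole provider to go unnamed, or entries to be passed over, more often in one arm. This stands, and it limits the point to a possibility.

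A reader might go further in three ways that the document does not support:

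- That every event depends on the mother's recall. It does not; her answer determines which records are opened.
- That intervention families have up to six contacts at which visits could come to light, against three in control. The three programme visits are described as education, coaching and cessation support. Nothing says that clinic attendance is asked about there, and the four-month question covers the same early period in both arms.
- That the Blinding section restricts assistants to minor outcomes and so flatly contradicts the Outcome measures section. It says they are responsible for collecting minor outcomes; it does not say these are all they collect. The retrieval role is left out there, not denied.

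Finally, a Manual of Procedures and Standard Operating Procedures are mentioned but not shown, and may fix the search in more detail. The absence of a provider list from an article is therefore not itself a fault. The point rests on what the article does state: the label and the route by which events are found.

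**Conclusion.** The double-blinded description is inaccurate. What the article describes is blinded adjudication and blinded analysis of records whose retrieval is not blinded. Differential capture of events is therefore possible. It is not demonstrated, its direction cannot be told from the document, and the check against source data would not detect providers or visits that were never named or copied.

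No size can be given from the document. Under an assumed 5% shortfall in the intervention arm, a Poisson count with control mean 3 and N = 380, a null effect would read as RR 0.95 with about 14% rejection. An excess of the same order would instead cost power. Neither figure should be taken as evidence that the trial's result is biased. The wording should be corrected and the search made uniform; no change in sample size follows.

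**What to change.** - For every infant, search the same prespecified set of main regional hospitals and clinics over the same dates, plus any provider the caregiver names, and copy all presentations in the window. If the Manual of Procedures already requires this, the article need only say so.
- In the copies sent to the adjudicating clinicians, mask mentions of the programme, the home visits or NRT. De-identification is planned but is not stated to cover these.
- Describe the outcome as record-based with blinded adjudication, not double-blinded.
- State in the Blinding section that unblinded research assistants retrieve the primary-outcome source records.

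Issuing search lists without the arm shown would not help with assistants who attended the home visits; the protection comes from applying the same search to everyone. The uniform search also leaves caregivers aware of their arm, and their decision to seek care remains part of the outcome, which is a further reason to correct the label.

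The cost is some additional record searching by existing staff. Consent for access to the infant's health records is already an inclusion criterion.
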